### Trial preparation

#### Training and supporting research staff

Prior to trial commencement, all research staff were subject to Disclosure & Barring Service checks (in the UK) and Criminal Record checks (in Japan). Research staff also completed ethics training (from the project’s internal ethics board), methods training (from CP) and pre-selected relevant online courses produced by Advinia Health Care (in the UK site) and by HISUISUI (in Japan site) for their care home staff. Staff also had weekly supervisory meetings, encouraged to keep a personal reflective diary, and reminded to contact project colleagues for additional support during the implementation of procedures in relation to ethical, methodological and/or technical issues and queries that emerged.

#### Care home staff preparation

A brief presentation was arranged with care home staff at a convenient and appropriate time to prepare them for what to expect during the testing procedures and to request that they continue their jobs as usual and to not rely upon the robot for any reason or change the usual provision and standard of care provided. This was to reduce the risk of confounding outcomes (e.g. because of a potential drop or change in the way that participants received care from their staff) and for ethical reasons (e.g. a reliance on the robot or decline in provision/quality of care could negatively affect participants). To help protect staff morale and concerns about the implications of technological interventions, staff were reminded that CARESSES is about understanding whether and how such interventions may improve outcomes in conjunction with current care rather than replacing care. Leaflets that conveyed this key information were distributed during the presentation and left in the main staff office for staff members who are unable to attend.

#### Pre-trial meeting with participants

A brief informal meeting was arranged with participants allocated to the experimental group or control group 1 to collect key personal information required to customise the robot including name, age and the names and contact information of informal carers that the robot could use to contact if called upon by the resident. A reminder card was also provided that stated when the first testing session shall take place. Any remaining questions prior to the first testing session were also addressed.

#### Technical preparation

Technical preparation and set-up procedures took place within each participant’s bedroom. This was necessary to install the required equipment (including networking, the robot, a small docking station, a video camera and microphone for monitoring), to map the bedroom space and to make note of objects of relevance (e.g. wardrobe) that the robot may draw attention to during interactions as appropriate. This required approximately 1 h to complete and was conducted in the presence of the resident or without their presence if they prefer and provide consent for. The specific robot hardware used in the study was the Pepper robot; a human-shaped robot manufactured by SoftBank Robotics. It is 4 ft tall and weighs 63 pounds.

#### Boosting standardisation between sites

To boost standardisation of procedures between the UK and Japan based sites, a number of procedures took place. First, a highly detailed protocol had been produced between the lead partners of both sites. In addition, to aid the development of the protocol, informal visits of candidate care homes in different sites had been made by the lead partners of both sites. Third, pre-existing validated Japanese translations of research instruments had been selected where possible, with all other relevant documents undergoing professional translation. Fourth, researchers from both sites had undergone the same ethics and methods training procedures and took part in a number of additional preparatory meetings, both in person (during yearly pre-planned project meetings) and online using Zoom videoconferencing software. Fifth, the Japanese procedures commenced 3 months after the commencement of procedures in the UK. This helped to ensure that any unanticipated required procedural changes could be considered and planned for prior to Japanese testing. Finally, step-by-step manuals to aid implementation of technical and methodological procedures between sites had also been produced.

### Interventions

#### Experimental group – CARESSES experimental robot

Participants allocated to this group received a CARESSES experimental robot for 2 weeks. This robot was culturally aware and thus aware of the resident’s cultural background prior to testing commencing. Therefore, it pre-loaded the appropriate Cultural Knowledge Base (CKB) and applied it during its time with the resident. During the first week, the robot interacted and provided culturally competent assistance on a culture-specific level only i.e. it did not learn and adjust to the participants’ individual values and preferences. In week 2, the robot was configured to be able to learn and adapt to the individual’s cultural profile thus moving from a culture-specific approach to a personalised approach. Its learning included ‘propagation’ i.e. personalised adjustments to the CKB in one area automatically lead to appropriate knowledge adjustments in other related areas. The specific functionalities of the robot included ‘chit-chatting’ (conversations about topics of interest and cultural relevance), setting reminders, playing music and videos, reading out audiobooks, making audio or video calls to informal carers and sending text messages and pictures to them, and contacting formal care staff members. It could also offer privacy (by turning away from the resident and looking down at the floor), display a news or weather report, suggest dressing and clothing options (moving to the wardrobe, talking about clothes, showing pictures of clothes, showing videos of wearing clothes), assisting with religion and prayer (reminding them to take the required objects, suggesting an appropriate place, reminding them what rituals are), assisting with meals (talking about food, showing images of meals, showing care home menus), control a smart light, play simple games, tell jokes, and enter a relaxation mode (relaxing music and relaxing scenes).

#### Control group 1 – CARESSES control robot

Participants allocated to control group 1 received a CARESSES ‘control’ robot for 2 weeks. This robot was not aware of the resident’s cultural background prior to the testing commencing. Rather, it pre-loaded a generic and more limited CKB that was not tailored for any particular culture-specific profile. In week 1, the robot did not learn and adjust to the participants’ individual cultural values and preferences. In week 2, however, the robot was configured to be able to learn and adapt to the individual’s cultural profile thus moving to a personalised approach. This robot’s learning did not include propagation but did possess the same suite of functions as the CARESSES robot although was less likely, in theory, to offer these in a culturally competent way. Because of the novelty of this type of research experiment, it remained unknown as to whether limiting the CKB, preventing propagation of learning and being culturally non-aware at the outset of interactions would indeed lead to poorer outcomes compared to the CARESSES robot (thus ensuring clinical equipoise).

#### Control group 2 – care as usual

Participants allocated to this group did not receive a robot and continued to receive care as usual.

#### Testing procedures

Each participant allocated to the experimental group or control group 1 had six sessions with the robot, each of which may lasted for up to 3 h. Sessions 1–3 were spread across week 1 (e.g. Monday, Wednesday, Friday) and sessions 4–6 were spread across week 2. The specific timings of these sessions were discussed and agreed with by the resident so that they took place at convenient times that, as much as possible, did not conflict with pre-existing planned activities. If a session lasted for less than 45 min, then this was considered a part 1 of 2 session. However, because of logistical and timing constraints, no more than 2 parts of one session could take place even if part 2 again lasted for less than 45 min. A minimum session threshold of 45 min was set because this was considered to be, theoretically, a reasonable minimum amount of time for a participant to potentially benefit from having access to the robot (an estimation partly based on the pre-trial pilot).

Session 1 consisted of a training session during which a researcher informed and guided a participant on how to use the robot and its functionalities (including what the robot can and cannot do), how best to communicate with the robot and how and when to request assistance. The remaining 5 sessions allowed the participant to use the robot independently and privately although all sessions were audio-video monitored for safety and scientific purposes (which participants were aware of). For these sessions, a researcher may have been present if requested by the participant and until he/she felt comfortable with interacting independently. Participants were also reminded that they may use the robot as much or as little as they wish and that they were free to leave their bedroom area for as long as they wish. A session was ‘live’ so long as the system was not suspended or turned off (due to technical problems, a desire by the participant to switch the system off or because the participant starts an activity which the research team considers unethical to continue to visually monitor).

During all sessions, a researcher and technician was present outside the participants’ bedroom to provide guidance and support when requested, and to intervene if the monitoring process identified any technical problems or concerns that may have jeopardised the participant’s safety and well-being.

After the final session was completed, the participants were debriefed and thanked. If the participant expressed sadness, upset and/or distress, the researcher provided company and support until their well-being had been observed to improve. In addition, a researcher also telephoned each participant 1 and 3 weeks after testing was completed for an informal conversation in part to assess whether any sadness or distress as a result of missing the robot had remained, in which case this was brought to the attention of the appropriate formal carer. Researchers were provided support to conduct these procedures during their ethics and methods training sessions, and had access to additional ongoing support and guidance from their supervisors (CP, LB).

### Data collection

Research measurements were performed during baseline (T0), after 1 week of testing (T1) and after 2 weeks of testing (T2) among resident participants and informal carers. The specific instruments that were employed (via quantitative structured interviews in all cases) were:
Cultural Competence Assessment Tool – Robotics (CCATool-Robotics). This is an adapted version of the RCTSH Cultural Competence Assessment Tool (CCATool) [16]. The tool measures older adults’ perceptions of the robot’s cultural awareness, cultural knowledge, cultural sensitivity, and cultural competence. This was completed by resident participants who receive a robot during T1 and T2.Short Form (36) Health Survey version 2 (SF-36 v2). The SF-36v2 [17] is a widely used, reliable and validated multi-purpose, short-form health survey with 36 questions. It measures the following eight dimensions of health: general health, bodily pain, emotional role limitation, physical role limitation, mental health, vitality, physical functioning and social functioning. This was completed by all resident participants and informal carers during T0 and T2.Short Form University of California Los Angeles (UCLA) Loneliness Scale (ULS-8). Loneliness was measured using the widely used and validated Short-Form Measure of Loneliness [18]. The scale is comprised of eight items to assess loneliness using a 4-point Likert scale with values ranging from “never” to “always”. This was completed by all resident participants and informal carers during T0 and T2.Negative Attitudes towards Robots Scale (NARS). This scale assesses participants’ attitudes towards robots [19]. NARS is comprised of 14 items scored on a 5-point agreement Likert Scale which measure three attitudinal domains: ‘Situations of interaction with robots’, ‘Social influence of robots’ and ‘Emotions in interaction with robots’. This was completed by all resident participants and their informal carers during T0 and T2.The Zarit Burden Inventory (ZBI). The ZBI consists of 22-items on a 5-point Likert Scale that measure subjective care burden among informal carers [20]. Its validity and reliability have been widely established. The scale items examine burden associated with functional / behavioural impairments and care situations. This was completed by all informal carers during T0 and T2.Questionnaire for User Interface Satisfaction (QUIS). The QUIS instrument uses a 9-point scale to measure users’ overall satisfaction of a technological system and its interface [21]. Some of the original statements were amended to assess the ease of use and usability of a robot. Thiswas completed by resident participants who received a robot during T2.

Qualitative one-to-one semi-structured interviews were also conducted with residents, and their informal carers, allocated to receive a robot. An interview schedule had been designed to elicit discussions related to: perceptions of the robot’s cultural competence, acceptability of and satisfaction with the robot’s interactions, quality of service provided, and impact the robot had upon their health and well-being, independence and autonomy. The interviews were conducted by a researcher who was already familiar with the participant. The researcher requested that the interview was audio-recorded (although this is not a requirement) and ensured that it took place at a convenient time for the resident or informal carer. For the latter, the option for interviews to take place over video-call or telephone were also made. Observations and reflections by the project team regarding the level of technical success, as well as any methodological/procedural or ethical issues and deviations during the study process were also collected and discussed during supervisory meetings or earlier if required with the project team.

### Data analysis

This work underpins the evaluation work package of the CARESSES study which shall be completed in early 2020. Quantitative data will be analysed using the IBM SPSS statistical software version 21.0 [22]. Kolmogorov-Smirnov tests will be initially conducted to establish the normality of the dependent variables. As appropriate, independent samples t-tests (for normal distribution), Mann-Whitney U tests (for non-normal distribution), or Chi-Square tests (normal or non-normal) will be used to compare the independent and dependent variables between the two groups/arms, in addition to simple descriptive statistics (means, medians and SDs as appropriate). For within-group repeated analyses, dependent t-tests (for normal distribution) and Wilcoxon signed-rank tests (for non-normal distribution) will be used to assess changes between pre-test and post-test scores. The level of statistical significance will be set at *p* ≤ 0.05. Linear mixed models will be used to assess the magnitude of differences in changes between the experimental and control groups. Drop out and intention-to-treat analyses will also be conducted. Fidelity will be assessed through a fidelity implementation checklist to be completed by the research team as the procedures take place. To assess cost-effectiveness, the EU MAFEIP (Monitoring and Assessment Framework for the EIP on Active and Healthy Ageing) tool will be used to estimate lifetime incremental quality-adjusted life years (using SF-36 data) with incremental cost of our intervention (compared against costs of care alternatives).

Qualitative data will be transcribed verbatim, entered into NVivo software Version 10.0 [23] and analysed using thematic analysis as described by Braun and Clarke [24]. This will involve two researchers independently reading and re-reading the transcripts to familiarize themselves with the data and independently labelling the data into categories and codes. Meaningful patterns across all the codes that are identified will be sorted into themes. All the codes under each theme will then be reviewed to confirm the validity of each theme and to produce overarching themes.

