**Method:**

This study employed a mixed-method, single-blind, parallel-group controlled before-and-after experimental trial design that took place in England and Japan. It aimed to recruit 45 residents of long-term care homes aged ≥65 years, possess sufficient cognitive and physical health and who self-identify with the English, Indian or Japanese culture (*n* = 15 each). Participants were allocated to either the experimental group, control group 1 or control group 2 (all n = 15). Those allocated to the experimental group or control group 1 received a Pepper robot programmed with the CARESSES culturally competent artificial intelligence (experimental group) or a limited version of this software (control group 1) for 18 h across 2 weeks. Participants in control group 2 did not receive a robot and continued to receive care as usual. Participants could also nominate their informal carer(s) to participate. Quantitative data collection occurred at baseline, after 1 week of use, and after 2 weeks of use with the latter time-point also including qualitative semi-structured interviews that explored their experience and perceptions further. Quantitative outcomes of interest included perceptions of robotic cultural competence, health-related quality of life, loneliness, user satisfaction, attitudes towards robots and caregiver burden.

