## Methods

### Study design

A mixed-method, single-blind, parallel-group controlled before-and-after experimental trial with 1:1 participant allocation was employed between March and November 2019 within eligible long-term older adult care homes in England and Japan. The care homes were predominantly those owned by Advinia Health Care (a full research partner in the project) from which English and Indian residents were recruited, and also within the HISUISUI assisted living facility in Japan from which Japanese residents were recruited. The testing procedures took place within participants’ bedrooms only. A pre-trial pilot study was successfully employed in November and December 2018 in one UK-based care home that assessed the feasibility, acceptability and fidelity of the intervention and its procedures. This led to a range of procedural and technical improvements made prior to the commencement of the full trial.

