### Participants

A total number of 45 residents of older adult long-term care homes, who self-identify themselves as primarily belonging to English (*N* = 15), Indian (N = 15) or Japanese (N = 15) cultures were aimed to be recruited within the UK (*N* = 30) and Japan (N = 15). The other eligibility criteria for participating residents were:
Aged ≥65 years.Resided in a single occupancy bedroom / bedroom area.Unlikely to express aggression towards themselves, the robot, and/or the researcher.Possessed sufficient cognitive competence.Possessed sufficient physical health.Able to verbally communicate in English (UK site only) or Japanese (Japan site only).

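### A Kolmogorov-Smirnov pre-test at about 15 residents per arm cannot establish normality, so the simple tests have no fixed method or effect measure

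*Protocol article*

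**What the plan says.** The rule is in the Data analysis section of the protocol article. It opens with the pre-test: "Kolmogorov-Smirnov tests will be initially conducted to establish the normality of the dependent variables". Between groups the choice is "independent samples t-tests (for normal distribution), Mann-Whitney U tests (for non-normal distribution"). Within groups, "dependent t-tests (for normal distribution) and Wilcoxon signed-rank tests (for non-normal distribution) will be used to assess changes" from before to after. Summaries follow the same logic: "simple descriptive statistics (means, medians and SDs as appropriate"). Chi-square is listed in the same sentence as the between-group tests.

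The section then plans linear mixed models, separately, to estimate how far the arms differ in change. These are not tied to the pre-test. No analysis is named as the main one. The significance level is 0.05. The section does not say whether the pre-test is run per arm or on pooled data, at what level, or with which critical values.

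On size, the Abstract states: "Participants were allocated to either the experimental group, control group 1 or control group 2 (all n = 15"). Table 1 gives 5 residents and 5 informal carers per arm in each culture, which again makes 15 per arm.

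**The concern.** A normality test that does not reject is evidence of normality only if it would probably have rejected otherwise. At 15 per arm, that is doubtful. If the test often misses real departures and sometimes flags normal data, it sorts outcomes into t-tests and rank tests partly by chance. The two families compare different quantities: a mean difference in one case, the rank ordering of two groups in the other. Neighbouring scores, such as two SF-36 dimensions, could then be reported on different footings for no substantive reason.

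The pre-test also looks at the wrong object. A two-sample t-test concerns the distribution within each arm (the residuals), and a paired t-test concerns the differences. The article names the dependent variables themselves.

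This matters because the first objective asks to what degree outcomes improve, and the Discussion calls the results preliminary. In such a trial, comparable effect estimates with intervals are the main quantitative product.

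**Working it through.** The article gives no SD, effect size or outcome distribution, so there is no figure of its own to reproduce. The design counts agree: 3 arms x 15 = 45, and 9 arm-by-culture cells x 5 = 45.

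**Inputs.** From the article: 15 per arm, significance level 0.05, and the selection rule above. Assumed: two-sided tests, a pre-test level of 0.05, and the outcome shapes below, which were varied for that reason. The 8-item sum imitates the ULS-8 (eight items, four points) with skewed, correlated items. There were 20,000 simulated samples per shape.

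**Step 1: power of the pre-test.** The statistic is D = max |Fn(x) - Phi((x - mean)/SD)|, with mean and SD estimated from the sample. At n = 15 the 5% critical value is 0.219 with the Lilliefors correction and 0.338 without it. At n = 45 the values are 0.131 and 0.198.

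| Assumed shape | Lilliefors, n = 15 | Uncorrected, n = 15 | Lilliefors, n = 45 |
|---|---|---|---|
| Normal | 4.7% | 0.01% | 5.1% |
| Uniform | 8.2% | 0.0% | 22.8% |
| Gamma, skew 1.0 | 14.3% | 0.1% | 37.4% |
| t, 3 df | 21.6% | 1.8% | 45.4% |
| 8-item sum | 22.8% | 0.3% | 76.2% |
| Gamma, skew 1.41 | 24.7% | 0.4% | 64.6% |
| Exponential, skew 2 | 45.1% | 1.8% | 93.7% |
| Lognormal, sigma 1 | 64.7% | 9.9% | 99.1% |

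The n = 45 column assumes the same distribution in all arms. If the arms differ, pooled data are a mixture, and their shape is not the one a t-test needs.

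**Step 2: how often the choice switches.** Suppose Lilliefors is applied in each of two arms and Mann-Whitney is used if either arm rejects.
- 8-item sum: 1 - (1 - 0.228)^2 = 0.404; simulated 40%. The same trial repeated would use Mann-Whitney 40% of the time and the t-test 60%.
- Normal data: 1 - 0.95^2 = 0.0975; simulated 9.5% switch without reason.
- Normal data, one test per outcome, outcomes taken as independent: at least one false rejection has probability 1 - 0.95^8 = 0.34 for 8 outcomes and 1 - 0.95^12 = 0.46 for 12. Eight SF-36 dimensions, ULS-8 and three NARS domains make 12.

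**Step 3: type I error of the two-stage rule, 15 per arm, no effect.**

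| Shape | Overall | t-test, given pre-test passed | t-test always | Mann-Whitney always |
|---|---|---|---|---|
| Normal | 5.2% | 5.2% | 5.2% | 4.7% |
| 8-item sum | 5.2% | 5.0% | 4.9% | 4.5% |
| Gamma, skew 1.41 | 5.2% | 5.9% | 4.8% | 4.5% |
| Exponential | 5.5% | 7.5% | 4.6% | 4.6% |
| Lognormal | 4.9% | 9.7% | 3.6% | 4.5% |

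The remaining shapes gave 5.0-5.1% overall. The overall figure stays low because a pass is uncommon where the conditional error is high. For lognormal data about 12% of trials pass and 88% go to Mann-Whitney, whose error is then 4.3%: 0.12 x 9.7% + 0.88 x 4.3% = 4.9%.

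**The case against.** Several stronger readings are tempting, and the documents do not support them.

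- **That the p-values are broadly invalid.** Overall error is 4.9-5.5% in every shape tried. Only the conditional t-test error rises, and only under strong skew; for the ULS-8-like sum it stays at 5.0%.
- **That the trial has no consistent effect estimate.** The Data analysis section plans linear mixed models for differences in change, outside the pre-test. The defect is confined to the simple between-group and within-group tests.
- **That the choice of test is always close to random.** This depends on the version of the test, which the article does not give. Uncorrected, the pre-test almost never fires at n = 15 and the t-test becomes the method by default. The choice is then stable, but normality has not been established.
- **That n = 15 is certain.** The article does not say per arm. Pooled over 45, the test detects strong skew well, but still finds only 37% at skew 1.0.
- **That results become non-comparable across time points.** Only CCATool-Robotics is measured at two post-baseline times.
- **That chi-square is a material error.** The sentence is qualified as to appropriateness, and every listed instrument yields a scale score. Expected counts of 15 x p do fall below 5 when the pooled proportion p is under one third, but this touches only incidental categorical tables.

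The article also admits that the trial lacks power. It is fair to say that an article condenses a fuller plan, but here it states the selection rule outright, so the rule can be judged.

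**Conclusion.** The concern holds for the simple between-group and within-group tests. At about 15 per arm the pre-test cannot do what the article asks of it: power is about 8-65% with Lilliefors and about 10% or less without, over the assumed shapes. It also examines raw variables instead of residuals or paired differences. With Lilliefors, method and effect measure vary by chance, for example 40% against 60% for a ULS-8-like score.

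The cost is an unfixed method and effect measure, plus a conditional t-test error of about 7-10% under strong skew. It is not a material inflation of overall error, and it does not reach the mixed model. The percentages rest on assumed shapes, a 5% pre-test level and, unless stated, per-arm testing. The change is worth making because it is cheap and consistent estimates are what this trial can offer.

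**What to change.** Delete the Kolmogorov-Smirnov step and fix one effect measure per scale in advance.

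- **Scales with T0 and T2 (SF-36, ULS-8, NARS, ZBI):** make the planned linear mixed model the single between-group analysis, or an equivalent baseline-adjusted model with culture and gender. Use small-sample degrees of freedom and report the adjusted mean difference with a 95% CI.
- **CCATool-Robotics (T1, T2) and QUIS (T2):** compare the two robot arms with the same model without a T0 term, since neither scale has a baseline.
- **Within-group changes:** describe them by the mean change with its 95% CI, without choosing a test from the data.
- **Checks:** inspect residuals, and run one pre-stated rank-based or stratified permutation analysis for every outcome as a sensitivity analysis.
- **Categorical tables:** use Fisher's exact test only where expected counts are small.

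The cost is analysis wording and one extra sensitivity run. No new data are needed.

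### For outcomes measured at T0 and T2, neither planned between-arm analysis is described as adjusting for the T0 score or gender, and nothing says which one carries the conclusion

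*Protocol article*

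**What the plan says.** All analysis statements are in the Data analysis section of the protocol article.

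- **Two-sample tests.** "As appropriate, independent samples t-tests (for normal distribution), Mann-Whitney U tests (for non-normal distribution", or chi-square tests, "will be used to compare the independent and dependent variables between the two groups/arms". No covariate is named. The text does not say whether T2 scores or change scores are compared, or which two of the three arms are meant.
- **Mixed model.** "Linear mixed models will be used to assess the magnitude of differences in changes between the experimental and control groups". Its covariates, and how it treats the T0 means, are not described.
- **Within-group tests.** Paired t or Wilcoxon tests "will be used to assess changes between pre-test and post-test scores".
- **Significance level.** "The level of statistical significance will be set at *p* ≤ 0.05". Sidedness is not given.
- **Population.** "Drop out and intention-to-treat analyses will also be conducted". The population for the other tests is not stated.

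The Data collection section says of SF-36 and of ULS-8: "This was completed by all resident participants and informal carers during T0 and T2". NARS follows the same schedule in residents and informal carers, and ZBI follows it in informal carers only. CCATool-Robotics (T1 and T2) and QUIS (T2) are completed only by residents who received a robot. Allocation and blinding gives gender as the stratification factor. The abstract gives the arm sizes: "Participants were allocated to either the experimental group, control group 1 or control group 2 (all n = 15").

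**The concern.** A T0 score is on file for the four outcomes that have a before-and-after schedule. In a comparison of arms this small, the T0 score is usually the most useful covariate available. The standard error of a chance T0 gap between two arms of 15 is √(2/15) = 0.365 SD, so sizeable imbalance can arise by luck alone. A two-sample test on T2 scores carries that imbalance straight into the result. A comparison of change scores subtracts the whole T0 gap, which over-corrects whenever the T0–T2 correlation is below 1 and the variances are equal. Adjustment for T0 removes only the part that predicts T2.

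Gender was important enough to stratify on, yet neither analysis is described as including it. Cultural group, which also sets the site and language in Table 1, is not included either.

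Finally, two between-arm analyses of the same outcome are planned with no order between them. If a Mann-Whitney test and the mixed model fall on opposite sides of 0.05, the article gives the reader no basis for choosing.

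**Working it through.** **The plan's own figure.** The article gives no power, effect size, SD or dropout rate, so there is no power calculation to reproduce. The sample size is consistent: 3 arms × 15 = 45, and 3 cultures × 3 arms × 5 = 45.

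**Inputs.** From the article: 15 per arm and a significance level of 0.05. Assumed: two-sided testing, 80% power, equal variances at T0 and T2, complete data, and a T0–T2 correlation r, which the article does not give.

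**Standard error of the arm difference, relative to T2 scores alone:**

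- T2 only: 1
- Change score: √(2(1 − r))
- Adjusted for T0: √(1 − r²)

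With two time points and complete data, a mixed model with unconstrained T0 means estimates exactly the difference in mean change, so the second line applies to it. If the T0 means are constrained to be equal across arms, the third line applies in essence.

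**Detectable difference.** This comes from the noncentral t distribution with 15 per arm and 28 df (27 df with the T0 covariate). The noncentrality is (difference ÷ factor) × √(15/2). For T2 only, 80% power needs 1.06 SD. The other results scale by the factor. At r = 0.7, for example, 1.06 × √0.60 = 0.82 and 1.06 × √0.51 = 0.76.

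| r (assumed) | T2 only | Change score | T0-adjusted |
|---|---|---|---|
| 0.3 | 1.06 SD | 1.25 SD | 1.01 SD |
| 0.5 | 1.06 SD | 1.06 SD | 0.92 SD |
| 0.7 | 1.06 SD | 0.82 SD | 0.76 SD |
| 0.8 | 1.06 SD | 0.67 SD | 0.64 SD |

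**Power at an illustrative 0.8 SD:**

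| r (assumed) | T2 only | Change score | T0-adjusted |
|---|---|---|---|
| 0.3 | 56% | 43% | 60% |
| 0.5 | 56% | 56% | 68% |
| 0.7 | 56% | 78% | 84% |
| 0.8 | 56% | 92% | 94% |

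**In terms of sample size.** Against T2 only, adjustment is worth 1/(1 − r²): 1.33, 1.96 and 2.78 times the sample at r = 0.5, 0.7 and 0.8. Against change scores it is worth 2(1 − r)/(1 − r²) = 2/(1 + r): 1.33, 1.18 and 1.11 times.

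For any r strictly between 0 and 1, the adjusted analysis is more precise than either alternative. Any further gain from gender and cultural group is not counted here. The figures do not apply to CCATool-Robotics or QUIS, which have no T0. For ZBI they are a best case, because informal carers take part only if nominated and willing, so 15 per arm is not assured.

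**The case against.** The strongest reply is that the plan already uses T0. The mixed model compares change between arms, and the two-sample tests may themselves be run on change scores. This is right. A reader might infer that the between-arm tests ignore T0 altogether, and the text does not support that. The fair comparator for the gain is therefore the change analysis as well as the T2-only test. Against change scores the improvement is 0.82 to 0.76 SD at r = 0.7 and 0.67 to 0.64 SD at r = 0.8. Over an interval of only two weeks, correlations of that order are plausible, though the article gives none.

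A second reply is that an article condenses a fuller document, which may give the model's covariates. That limits the point to the analyses as described. It does not remove it, because the article does commit to two-sample tests, which cannot carry covariates, beside a model of change, with no order between them.

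Third, the trial says that it lacks power and that its results are preliminary, and in a randomised comparison both change scores and T0 adjustment are unbiased. Both statements are true, so this is a matter of efficiency and clarity and not of validity. A small trial still gains from using its data well.

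A reader might also infer from the word "also" in the intention-to-treat sentence that the other tests exclude dropouts, so that dropout could decide the main result. The documents do not support this. No comparison is designated as main, the other tests are nowhere called completer analyses, no dropout rate is given, and a likelihood-based mixed model can keep participants with partial data. What remains is narrower: the population for the other tests is not stated.

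**Conclusion.** The point holds as an improvement that costs nothing. For SF-36, ULS-8, NARS and ZBI, neither between-arm analysis, as described, adjusts for the T0 score or for the stratification factor, and nothing says which one carries the conclusion.

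The size depends on an assumed correlation. If the two-sample tests use T2 scores alone, adjustment lowers the detectable difference from 1.06 SD to between 0.92 and 0.64 SD over r = 0.5 to 0.8. Against a change analysis the gain is 0.14 SD at r = 0.5, 0.06 SD at 0.7 and 0.03 SD at 0.8. Below r = 0.5, change scores do worse than T2 scores alone. If the mixed model already constrains the T0 means to be equal, most of the precision gain is already there, and what is left is the missing gender term and the missing order between the analyses.

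The population question is secondary, and its effect cannot be computed from the article.

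**What to change.** - **Outcomes with a T0 score.** Name one between-arm analysis: T2 score on T0 score, arm (three levels), gender and cultural group, or a mixed model with a common T0 mean and the same factors. Fit it to residents and to informal carers separately.
- **Population.** State that this analysis takes participants as allocated, and label any completer analysis as a sensitivity analysis.
- **Two-sample tests.** Keep the t and Mann-Whitney tests as supportive only. Add a rank-based or bootstrap check of the main model if its residuals are clearly non-normal, so that non-normal scores remain provided for.
- **CCATool-Robotics and QUIS.** Compare the two robot arms only, adjusting for gender and cultural group. The T1 score of CCATool-Robotics is taken after a week of robot use, so it should not stand in as a baseline covariate.

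The cost is wording. The article describes the analysis as still to be done, all the variables are already collected, and the named software fits these models.
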